#### Self-reported health status

The EQ-5D is a generic measure of self-reported health status [32] and provides the information required to generate utility values for estimating quality-adjusted-life years (QALYs), the measure of outcome used in cost-utility analyses. The EQ-5D has been found to have acceptable reliability and validity in elderly patients [33,34].

#### Use of healthcare services

Summary information on the use of general practitioner services and inpatient hospital care, from general practitioner and New Zealand Health Information Service records, were obtained for the year prior to intervention and compared with the year following intervention delivery. Use of all other health services and any personal costs associated with the physical activity regime were collected on the monthly diaries described above.

#### Pedometer usage

At the end of the intervention (3 months) and at the 12 month follow-up a series of questions regarding pedometer usage were asked of all participants [35]. Questions related to knowledge of pedometers, wearing patterns over the previous period, and whether participants felt that the pedometer helped them increase their level of physical activity.

### Sample Size

Based on means, standard deviations, and change from previous trials, a sample of 137 per group would have at least 80% power at the 0.05 level of significance to detect a true difference in the change between the two groups of 5 points on the general health domain score of the SF-36, 1 hour of moderate physical activity, and a detectable difference of 15% of people meeting physical activity guidelines. To allow for an attrition rate of approximately 20% over 12 months, 165 participants were required in each group.

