
After making suitable arrangements, the Research Officer visited the patient in their home to answer any additional questions on the study, provide the information sheet, obtain informed consent, book a general practitioner appointment for commencement of the intervention, provide a falls and injuries calendar and reply-paid envelopes, and then take the following baseline measures: demographics questionnaire, blood pressure and current blood pressure medications (if applicable), lower extremity function measures, quality of life, physical activity, depressive symptoms, and self-reported health status.

During the general practitioner visit, the patient was randomized into either the standard Green Prescription or the pedometer Green Prescription group and commenced on the intervention through the initial prescription of physical activity. Those in the pedometer group were issued with a pedometer by the general practitioner or practice nurse and instructed in its use. At the end of the appointment the Green Prescription was faxed to the local Regional Sports Trust for continuation of the intervention. The Regional Sports Trust is as government-funded organization involved in provision of sports and physical activity opportunities and programs for the population of that region. General practitioners and other relevant practice staff participated in training relating to the administration of the intervention.

Recruitment was undertaken over 17 months from July 2006 to December 2007 to allow for the interventions to be delivered during all seasons. A total of 330 people were recruited into the trial. At 3 months, 278 remained in the study with 270 remaining at 12 months. Included in the 330 recruited participants were 31 couples (defined as living in the same household). In order to reduce the effects of contamination both individuals in the couple were allocated to the same intervention and were treated as clusters for the purposes of statistical analysis.

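### The 20% attrition allowance is miscalculated (165 per group is 137 × 1.2; 137/0.8 gives 172), and no allowance for co-allocated couples is stated

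*Protocol article*

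**What the plan says.** The Sample Size section of the protocol article says that "a sample of 137 per group would have at least 80% power at the 0.05 level of significance". The power claim covers three targets: "5 points on the general health domain score of the SF-36", "1 hour of moderate physical activity", and a 15% difference in the share of people meeting activity guidelines. The first is framed as a "true difference in the change between the two groups". The section refers to previous trials for means and SDs but prints none, and it gives no control rate. It then inflates the number: "To allow for an attrition rate of approximately 20% over 12 months, 165 participants were required in each group".

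The Recruitment section reports that 330 people were recruited. On retention it says: "At 3 months, 278 remained in the study with 270 remaining at 12 months". On households it says: "Included in the 330 recruited participants were 31 couples (defined as living in the same household"). Both members of a couple went to the same arm and are treated as a cluster in the analysis.

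The Analysis section plans intention-to-treat comparison with mixed-effects or GEE models that take account of repeated measures and natural clustering, with multiple imputation where needed.

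**The concern.** Two steps in the sample-size paragraph do not secure the 137 evaluable participants per group to which the power claim is attached.

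- **Attrition.** To have 137 left after losing 20%, one divides by 0.8. Multiplying by 1.2 adds 20% of the smaller number, which is not enough. The stated 165 matches the multiplication.
- **Couples.** Members of a household allocated to the same arm carry less independent information than the same number of unrelated people. The paragraph mentions no design effect.

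What is at stake is how a null result is read. Readers will judge it against a power of at least 80%, resting on a sample size that does not follow from its own inputs.

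**Working it through.** **Inputs from the article:** 137 per group; 0.05 significance level; about 20% attrition; 165 per group; 330 recruited; 278 remaining at 3 months and 270 at 12 months; 31 couples.

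**Assumptions:** a two-sided test (sidedness is not stated), even losses between arms, the same share of couples among those retained as among those recruited, and the ICC values shown.

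**1. Reproduce the stated figure.** 137 × 1.2 = 164.4, rounded up to 165. This matches exactly.

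**2. Correct inflation.** 137/(1 − 0.20) = 171.25, so 172 per group (344 in total). That is 7 more per group than stated.

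**3. What 165 secures.**
- At 20% attrition: 165 × 0.8 = 132, which is 5 short of 137.
- Largest attrition that still leaves 137: 1 − 137/165 = 17.0%.
- Observed: 1 − 270/330 = 18.2%, and 270/2 = 135 per group.

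**4. Power if 137 was the exact minimum for 80%.** By the normal approximation, the standardised effect is d = (1.960 + 0.842) × √(2/137) = 0.3385, and power at n per group is Φ(d√(n/2) − 1.960).
- n = 135: Φ(2.781 − 1.960) = 79.4%.
- n = 132: Φ(2.750 − 1.960) = 78.5%.

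**5. Couples.** There are 62 people in couples and 330 − 62 = 268 singles. The participant-weighted mean cluster size is (268 × 1 + 31 × 4)/330 = 392/330 = 1.188, so the design effect is 1 + 0.188 × ICC.

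| Assumed ICC | Design effect | Effective n from 132 | Power from 132 | Power from 135 |
|---|---|---|---|---|
| 0 | 1.000 | 132.0 | 78.5% | 79.4% |
| 0.1 | 1.019 | 129.6 | 77.8% | 78.7% |
| 0.3 | 1.056 | 125.0 | 76.3% | 77.2% |
| 0.5 | 1.094 | 120.7 | 74.8% | 75.8% |

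The required number with both allowances, 137 × design effect/0.8, is 175, 181 and 188 per group at ICC 0.1, 0.3 and 0.5.

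**6. How much headroom would remove the shortfall.** If the true power at 137 was 81.4% or more, 132 still gives 80%. With couples included, the power needed at 137 is about 83.5% (ICC 0.3) or 84.7% (ICC 0.5).

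**7. Dependence on the missing control rate.** For the 15-point difference, power at 132 per group is 83.5% for 15% versus 30%, 78.2% for 20% versus 35%, and 74.2% for 25% versus 40%.

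**The case against.** The best defence has four parts.

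- **Headroom.** The claim is *at least* 80%, and one number serves three outcomes, so some of them probably have power to spare. This stands. A reader might infer that 165 per group fails to deliver 80% power. The article does not support that, because step 4 takes the worst case in which 137 was the exact minimum, and the inputs needed to check this are not printed.
- **Size.** The attrition slip alone costs at most about 1.5 points in that worst case, and 0.6 at the observed retention. The 20% is also given only as approximate, and 165 covers 17.0%. The size argument stands. The rounding argument is weak, since 165 is exactly what multiplying by 1.2 gives.
- **Partial data.** The planned models and imputation use more than completers, so a two-sample comparison of 132 per group is not the planned analysis. This is true in principle, but the gain is probably small. Of the 60 people lost by 12 months, 330 − 278 = 52 had gone by 3 months and only 278 − 270 = 8 left later, if no one returned. Most of those lost therefore have only baseline data.
- **Couples.** The number of couples is reported as a result of recruitment, only 62 of 330 people (19%) are affected, and an allowance inside the 137 cannot be excluded from a condensed article. This stands too. A reader might infer that the trial ignores the pairing, but the Recruitment and Analysis sections both provide for it in the analysis. What is not stated is an allowance in the sample size.

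**Conclusion.** The arithmetic error is certain: for 20% attrition the figure should be 172 per group, and 165 secures 132. The observed 18.2% attrition was better than planned and still leaves about 135 per group, below 137, if losses were even.

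The effect on power is small and conditional. Attrition alone brings it to 78.5% at 132 or 79.4% at 135, if 137 gave exactly 80%. Adding couples takes the figure at 132 to about 78% to 75% for an ICC of 0.1 to 0.5. That range is an assumption; the article gives no ICC. None of these figures should be quoted as the trial's actual power.

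The wording on change in the Sample Size section might also be read as committing the trial to a change-score analysis. The Analysis section makes no such commitment. The point is a minor correction: no estimate, error rate or planned analysis changes.

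**What to change.** Restate the sample-size paragraph as follows.

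1. Say that 165 per group secures 132 at 20% attrition, and 137 only up to 17.0%.
2. Give the resulting power for each of the three outcomes, using the SDs and control rate that the trial took from earlier studies, and state the sidedness of the test.
3. Include the couple design effect, 1 + 0.188 × ICC, with the ICC stated as an assumption.

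Optionally, specify baseline adjustment (baseline as a covariate, or a common baseline mean) within the longitudinal models already planned. Relative to a change score, the variance is multiplied by (1 + ρ)/2, where ρ is the correlation between baseline and follow-up. If 137 was the exact minimum for a change-score comparison, then at 135 per group with a design effect of 1.094 (ICC 0.5) power would be about 87% at ρ = 0.5 and 82% at ρ = 0.7; both ρ values are assumptions. Household clustering is already planned and needs no new provision.

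The cost is one rewritten paragraph and, if the option is taken, one model term. Recruitment is complete, and no participants or data need be added.

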### Analysis

The primary analysis for this trial will be based on group allocation and the intention to treat principle. Apposite longitudinal methods, such as mixed-effects multilevel models and generalized estimating equation analysis will be used to compare the two treatment groups, accommodating the correlation between repeated observations and the natural clusterings and hierarchies in the sample [36]. Missing data will be assessed and multiple imputation undertaken, where necessary [37]. Model assumptions and diagnostics will be rigorously assessed [38].

An economic evaluation will form part of this trial. Incremental cost-effectiveness ratios will be calculated for selected outcome measures, such as cost per total energy expenditure achieved and cost per kilogram of weight lost, if any incremental change in outcome is statistically significant. For the cost-utility analyses, utility values will be calculated using the visual analogue scale of the EQ-5D. If the incremental gain in utility values is statistically significant, these utility values will be transformed into Quality Adjusted Life Years (QALY's) and the incremental cost per QALY will be calculated.

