In this study we aimed to compare the efficacy of a pedometer-based Green Prescription with the conventional time-based Green Prescription in increasing and maintaining physical activity levels in low-active older adults. As well, the trial sought to examine the effects of the interventions on health-related quality of life, functional status, blood pressure, weight status, and health care utilisation and costs. Incremental cost-effectiveness and cost-utility ratios will also be estimated.

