## Methods/Design

### Design

A randomized controlled trial design was used to investigate the efficacy and cost-effectiveness of a pedometer-based Green Prescription in improving physical activity levels and health outcomes in low active older adults compared with the usual (time-based) Green Prescription. Ethical approval to conduct the study has been granted by the Health and Disability Ethics Committees, Northern Y Regional Ethics Committee (Reference Number NTY/05/11/086).

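### Cost-effectiveness ratios and QALYs are calculated only after a statistically significant effect, which conflicts with the stated economic aim and selects for overstated effects

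*Protocol article*

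**What the plan says.** The second paragraph of Analysis sets two conditions. Ratios for selected outcomes, with total energy expenditure and weight as examples, are calculated as in "cost per kilogram of weight lost, if any incremental change in outcome is statistically significant". For the cost-utility analysis, "utility values will be calculated using the visual analogue scale of the EQ-5D", and then: "If the incremental gain in utility values is statistically significant, these utility values will be transformed into Quality Adjusted Life Years (QALY's"), after which the cost per QALY follows. The section does not say what is reported if a condition is not met.

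Elsewhere the economic question carries no condition. The last paragraph of the Background says "Incremental cost-effectiveness and cost-utility ratios will also be estimated". Design gives the trial's purpose as to "investigate the efficacy and cost-effectiveness of a pedometer-based Green Prescription".

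Sample Size says that "a sample of 137 per group would have at least 80% power at the 0.05 level of significance". Its two continuous targets are "5 points on the general health domain score of the SF-36, 1 hour of moderate physical activity". The binary target is stated separately, as "a detectable difference of 15% of people meeting physical activity guidelines". EQ-5D, weight, total energy expenditure and cost are not among these targets.

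**The concern.** Cost-effectiveness is a joint question about incremental cost and incremental effect. A test of the effect alone does not answer it, for three reasons.

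- **A non-significant effect is not a zero effect.** Two arms with similar effects can still differ in cost, and that difference may settle the choice. The trial collects a year of service use and personal costs, yet under this rule a cost difference alone releases no ratio.
- **The tests were not planned for.** Whether a ratio appears depends on outcomes for which the article gives no SD, expected difference or power.
- **The rule filters on the estimate.** A ratio is seen only when the estimated effect is large relative to its standard error. Released effects are therefore too large on average, and a ratio with a positive incremental cost tends to look too favourable unless power is high.

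The utility sentence also speaks of a gain, so read literally a significant utility loss in the pedometer arm would not lead to a cost-utility analysis. This applies to that sentence only. The condition on the other ratios refers to any change and covers both directions.

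At stake are whether a stated purpose of the trial is answered, and whether a published ratio can be taken at face value.

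**Working it through.** **The plan's own figure.** The article gives no figure for the economic evaluation. Its only power statement is 137 per group for at least 80% power at 0.05 (Sample Size). This cannot be reproduced independently, because no SDs or control rate are given. It can be solved backwards, taking the test as two-sided:

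- Standardised difference = (1.960 + 0.842) × √(2/137) = 2.802 × 0.1208 = 0.338 SD.
- This corresponds to an SD of 5/0.338 = 14.8 points for SF-36 general health, and 60/0.338 = about 177 minutes for one hour of activity.
- For the 15-point difference in proportions, 20% versus 35% requires 138 per group, so a control rate near 20% fits.

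The value of about 0.34 SD is what the trial was sized to detect on its own targets. It is a reference point here and not an expectation for EQ-5D.

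**Inputs for the check.** Recruitment reports 270 participants remaining at 12 months, which is 135 per arm if evenly split (assumed). The comparison is taken as a two-sample normal test, two-sided at 0.05, with no adjustment for baseline or for the 31 couples (assumed). The true difference d, in SD units, is unknown and is varied.

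**Formulas.**

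- SE = √(2/135) = 0.1217 SD.
- Smallest estimate that releases a ratio = 1.96 × 0.1217 = 0.239 SD.
- With m = d/SE, the chance that no ratio is released = Φ(1.96 − m).
- Mean overstatement of a released effect = 1 + φ(1.96 − m) / {m × [1 − Φ(1.96 − m)]}.

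For d = 0.20: m = 1.643, so Φ(0.317) = 0.624, and the overstatement is 1 + 0.379/(1.643 × 0.376) = 1.61.

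| True difference (SD) | Chance of no cost per QALY | Mean overstatement of released effect | Mean released ratio ÷ true ratio* |
|---|---|---|---|
| 0.10 | 87% | 2.99 | 0.34 |
| 0.20 | 62% | 1.61 | 0.64 |
| 0.30 | 31% | 1.21 | 0.87 |
| 0.34 | 21% | 1.13 | 0.94 |
| 0.50 | 2% | 1.01 | 1.05 |

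*Incremental cost held fixed and positive.

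The chance of no result is one half at about 0.24 SD.

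**Sensitivity to the SD.** If utility has an SD of 0.20 (assumed), a gain of 0.03 is 0.15 SD: 77% of trials would release no cost per QALY, and released gains would be overstated 2.06-fold. A gain of 0.05 would pass 54% of the time, with 1.36-fold overstatement. If adjustment for baseline and repeated measures brought the effective SD down to 0.14 (assumed), the same gains would pass 42% and 84% of the time, with 1.53- and 1.10-fold overstatement.

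**The case against.** The strongest defence is that a ratio with a denominator near zero is unstable, and that the authors are declining to publish one. The instability is real. It is a reason to present results on a scale that does not divide by the effect, and not a reason to withhold the analysis.

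It can also be said that the Background sentence is a general aim which the Analysis section then qualifies, and that the loss is limited: utility values are calculated regardless, service use is compared regardless, and nothing bars showing costs and effects side by side. This stands in part. What the rule withholds is the QALYs, the ratios and the joint uncertainty. But those ratios are exactly what the Background says will be estimated, so the two places do not agree as written.

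Three stronger readings are tempting, and the article does not support them.

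- **A reader might infer that the cost-utility question will most likely go unanswered.** That requires a true utility difference below about 0.24 SD. A small difference is plausible, since Control Group describes an active comparator that differs in one element. But the article gives no EQ-5D effect or SD, and at 0.34 SD only about 21% of trials would release nothing.
- **A reader might infer that every released ratio is materially biased.** Selection always acts on the effect estimate, but its size depends on power and is negligible by 0.50 SD.
- **A reader might infer that cost per QALY would be roughly halved.** That is one row of assumptions (0.15 SD, with fixed positive incremental cost) and not a general result.

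The article's failure to list every effect measure or graphical display is not a fault either, since a full analysis plan may hold that detail.

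**Conclusion.** The concern holds. The rule is stated twice as a decision, so it is not a matter of detail left to another document. Followed as written, it can withhold ratios that the Background promises without condition. It decides this by tests that the sample size does not cover, it ignores incremental cost, and it favours overstated effects among the ratios that appear.

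The size cannot be fixed from the article. It runs from 87% of trials with no cost per QALY and 3.0-fold overstatement at 0.10 SD to 2% and 1.01-fold at 0.50 SD. These figures rest on an even split of the 270, a two-sided test and an unadjusted comparison. The planned longitudinal models could improve precision, and clustering by couple could reduce it. The comparison of physical activity between the arms, the data collection and the sample size are unaffected.

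**What to change.** In Analysis, delete both conditions that require statistical significance. State that QALYs, incremental cost and incremental effect will be calculated and reported with their joint uncertainty whatever the p-value and whatever the direction of the difference.

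One suitable method is a bootstrap that resamples households, so that the couples stay together, summarised as net benefit over a range of thresholds or as an acceptability curve. Other methods that carry the joint uncertainty would serve equally well.

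The cost is a change of wording and a small amount of extra analysis. The price in reporting is that intervals may be wide or the result inconclusive, which is then the correct finding to publish. No new data or participants are needed.

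### QALYs are to be built from the EQ-5D visual analogue scale, which read plainly is a self-rating and not a preference-based utility, so any cost per QALY would not be a valid cost-utility estimate

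*Protocol article*

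**What the plan says.** Three places in the protocol article bear on this.

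- **Background, final paragraph (aims):** "Incremental cost-effectiveness and cost-utility ratios will also be estimated". A cost-utility result is therefore a stated aim.
- **Self-reported health status:** "The EQ-5D is a generic measure of self-reported health status" and it "provides the information required to generate utility values for estimating quality-adjusted-life years (QALYs), the measure of outcome used in cost-utility analyses". This gives the reason for including the instrument. It does not say which part of the instrument supplies the utilities, and it names no value set.
- **Analysis, second paragraph:** for the cost-utility work, "utility values will be calculated using the visual analogue scale of the EQ-5D". A condition follows, "If the incremental gain in utility values is statistically significant", and where it is met, "these utility values will be transformed into Quality Adjusted Life Years (QALY's) and the incremental cost per QALY will be calculated".

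No other section names a value set, a step that converts ratings to preference-based values, or a sensitivity analysis with index utilities.

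**The concern.** The EQ-5D has two parts. One is a five-dimension description of health, which a societal value set turns into a preference-based index. The other is a visual analogue scale on which respondents mark how good their own health is today. A QALY is time weighted by a utility on a scale where dead is 0 and full health is 1, and the weight is meant to reflect preferences. The self-rating asks for no trade-off and has no anchor at dead, so multiplying it by time does not give a QALY.

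The article justifies the EQ-5D by its ability to supply utilities, which is a property of the scored five-dimension profile, and then assigns that job to the other part. At stake is every cost-per-QALY figure the trial might report, and also the decision whether to report one.

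**Working it through.** The plan gives no EQ-5D score, standard deviation, utility gain or cost, so there is no figure to reproduce. The check consists of reading the sections together, followed by some algebra.

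**1. Which values become QALYs?** The Analysis section names the visual analogue scale as the source, and its next sentence carries those same values forward into QALYs. Nothing comes between the two except the significance condition. The general remark under Self-reported health status does not change this, because the Analysis section is the more specific text and fixes the source.

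**2. How does the choice of scale reach the ratio?**

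- Cost per QALY: R = ΔC / ΔQ, where ΔC is the incremental cost and ΔQ the incremental QALYs.
- Let the between-group gain on the rating scale (rescaled to 0–1) be k times the gain on the preference-based index. Then ΔQ(scale) = k × ΔQ(index).
- Hence R(scale) = ΔC / (k × ΔQ(index)) = R(index) / k.

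The documents give no value for k. The range below is an assumption for illustration only:

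| k (assumed) | R(scale) / R(index) = 1/k |
|---|---|
| 0.5 | 1 / 0.5 = 2 |
| 1 | 1 / 1 = 1 |
| 2 | 1 / 2 = 0.5 |

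Over this range the ratio could be doubled or halved, and nothing in the documents favours either direction.

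**3. How does it reach the significance condition?** The condition is applied to the gain in these same values. If the rating scale were just a constant multiple of the index, the gain and its standard error would scale together and the test result would not change. The two are different measurements, so the gain relative to its standard error can differ. The rating scale could pass where the index would not, or fail where the index would pass. The choice of scale therefore also governs whether a ratio exists to be reported.

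**4. What is untouched?** The comparison of physical activity and the clinical outcomes, the sample size (which rests on SF-36 general health, hours of moderate activity and the proportion meeting guidelines), and the cost-effectiveness ratios for energy expenditure and weight do not use EQ-5D values.

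**The case against.** **A different reading of the sentence.** Values calculated using the scale could loosely mean a societal tariff that was itself obtained from rating-scale valuations and is applied to the five-dimension responses. On that reading the utilities would come from the right part of the instrument, and what remained would be a request to name the tariff, a detail that a condensed article may leave to a fuller plan. This reading is possible, but it is not stated. The wording points to the scale belonging to the EQ-5D, and no tariff is mentioned anywhere. The plain reading is the stronger one, and the sentence needs changing on either.

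**It is a minor part of the trial.** The lead aim is physical activity, and the QALY step may never be triggered. Both points stand and limit the reach of the problem. They do not remove it, because cost-utility ratios are a stated aim and the trigger uses the same values.

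**Reliance on knowledge outside the article.** The article does not describe the visual analogue scale. That it is an unanchored self-rating is a property of the instrument and not something the text says. This is fair as a description of the argument's basis, and it is why the conclusion depends on the plain reading.

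**Stronger inferences that do not hold.** A reader might infer that, because participants know whether they use a pedometer, a global self-rating would be more inflated in that arm than the five-dimension items. The documents do not support this: both parts of the instrument are self-report, and both arms receive an active prescription and three calls. A reader might also infer that the cost per QALY would be biased in a known direction or by a known factor. No EQ-5D data are given from which to derive either.

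**Conclusion.** The concern holds for the cost-utility analysis. As written, the plan fixes a utility source that, read plainly, is not a preference-based utility, and it uses that source both for the QALYs and for the condition that releases them. A cost per QALY produced this way would not be a valid cost-utility estimate. This is a stated analysis choice and not a missing detail.

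The effect on the ratio cannot be quantified from the documents. Under the assumed k of 0.5 to 2, it would be a factor of 2 to 0.5.

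It would go too far to conclude that every economic result is affected or that a faulty cost per QALY is certain to appear. The ratios for other outcomes do not depend on this choice, and no cost per QALY is calculated unless the significance condition is met. The conclusion rests on two assumptions: that the sentence refers to the respondent's own rating, and that the full plan, not shown here, does not override it.

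**What to change.** Replace the sentence on utility values in the Analysis section with wording such as:

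> Utility values for the cost-utility analysis, including those used in the significance condition, will be derived from the five-dimension EQ-5D responses scored with [named published societal value set]. The visual analogue scale will be reported separately as a self-rated health outcome.

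If a societal tariff derived from rating-scale valuations was intended, name it there and say that it is applied to the five-dimension responses.

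The cost is one sentence and one scoring step. No new data are needed, provided that the five-dimension items were collected along with the scale. The article says the EQ-5D was used but does not list its parts, so this should be confirmed. The change should be made before utility values are compared between the groups.
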